### Follow up

Follow up will be performed until one year after surgery. Patients will be evaluated in the out patient clinic 2 weeks, 6 weeks, 3 months, 6 months and 12 months postoperatively. A figure of the follow-up schedule is visible in Fig. 1. Subjects can leave the study at any time for any reason if they wish to do so without any consequences. The investigator can decide to withdraw a subject from the study for urgent medical reasons. Table 1 represents the time schedule of enrolment, interventions and assessments.

**Fig. 1 Fig1:**
[figure not shown]
Follow-up schedule

**Table 1 Tab1:** Time schedule of enrolment, interventions and assessments

TIMEPOINT	Baseline	Day of surgery	Follow up					
	-t_1_	0	Day 1	2 wk	6 wk	3 m	6 m	12 months
ENROLMENT:								
Eligibility screen	X							
Informed consent	X							
*Demographics*	X							
Randomization		X						
INTERVENTIONS:								
Conventional wound closure		X						
Flap fixation using sutures		X						
Flap fixation using tissue glue		X						
ASSESSMENTS:								
Clinical assessment seroma and complications				X	X	X	X	X
Pain score				X	X	X	X	X
Patient reported cosmesis assessment				X	X	X	X	X
DASH	X			X	X	X	X	X
EQ-5D	X				X	X	X	X
Cost evaluation	X		X			X	X	X

## Blinding

Both patients and surgeons will be blinded with regard to if and which method of flap fixation is used. The surgeon performing the procedure is obviously not blinded; surgeons performing the assessments during follow up will be blinded to the closure technique. 30 min before closure patients will be randomized in the online randomization programme ALEA. A randomization number is issued and is duly noted in patients’ files. The operating report will not specify which method has been used. The following statement is noted at the end of the operating report:

‘The trial participant was randomized in 1 of the 3 treatment arms of the SAM Trial. For blinding purposes, this data has been stored in a secured database. In case of SAE or SAR, the method of wound closure can be revealed after contacting the primary investigator.

Postoperatively, patients are not informed of the method of wound closure that was used. Patients and surgeons will be questioned during every postoperative follow up appointment on the presumed method of closure. In this fashion, one will be able to assess whether double blind randomization is realistic upon evaluation. As patients and surgeons are blinded to the method of closure; seroma and its sequelae in trial patients will not be assessed by their own surgeons during follow up.

## Data management

Data is recorded on trial specific case report forms (CRF’s). The following patient demographics and characteristics were recorded: age, BMI, Charlson Comorbidity Index, use of anticoagulants, smoking, neoadjuvant chemotherapy, clinical node positivity, axillary lymph node clearance, TNM staging, specimen weight, mastectomy wound surface, drain output and drain time. To maintain anonymity, CRF’s are identified only by a randomization code. A data manager and research nurse regularly verify data and send queries for missing or inconsistent data. All data is stored in a database that is updated on a weekly basis.

## Sample size

The number of seroma aspirations is not normally distributed. Therefore, sample size estimations based on normally distributed continuous variables cannot be used. It is possible to use formulas based on non-parametric analysis methods, estimating the chance of a random patient in the treatment group having fewer aspirations than a random patient in the control group. However, since the majority of patients will have the same number of aspirations (i.e. 0), this method of sample size estimation does not seem to be applicable to our study. Sample size estimation based on ordinal regression is in line with the data distribution and limited possibilities (maximum number of aspirations in the observational retrospective study was 4) of the outcome variable (Walters SJ. Health Qual Life Outcomes 2004: 2(1); 26). Using alpha = 0.025 (correction for 2 comparisons with 3 study groups), beta = 0.10, and a proportional odds ratio = 2.67 (corresponding to an absolute difference of 20% in the need for seroma aspirations), the sample size is estimated at 112 patients per study group. Therefore a sample size of 336 is planned for. To recruit this sample size, a 40 month inclusion period is estimated.

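### The printed sample-size inputs do not reproduce 112 per group: with a two-sided 0.025 test and 40% against 20% the named method needs at least 118, and power at 112 is about 87%, not 90%

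*Protocol article*

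**What the plan says.** All the planning figures are in the Sample size section of the protocol article.

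- Error rates and effect: "Using alpha = 0.025 (correction for 2 comparisons with 3 study groups), beta = 0.10, and a proportional odds ratio = 2.67". The same sentence equates this odds ratio with a 20-point absolute difference in the need for aspiration.
- Shape of the outcome: a rank-based sample-size formula is set aside "since the majority of patients will have the same number of aspirations (i.e. 0"), and the "maximum number of aspirations in the observational retrospective study was 4". Ordinal regression is named as the basis of the calculation.
- Result: "the sample size is estimated at 112 patients per study group", and so 336 in total.

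The section does not say whether alpha is one- or two-sided. It gives neither the aspiration rate in each arm nor the assumed proportions with 0, 1, 2, 3 and 4 aspirations. It makes no allowance for loss. The Follow up section says that "Subjects can leave the study at any time for any reason if they wish to do so without any consequences".

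**The concern.** A reader should be able to put the printed alpha, power and effect into the named method and arrive near 112. Here the result falls to one side of 112 if the test is two-sided and to the other side if it is one-sided.

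This calculation is the only justification for 336 patients and for the 90% power on the primary outcome. A non-significant comparison of either fixation method with conventional closure will be read against that 90%, so the figure should match the effect beside which it is printed.

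**Working it through.** **Inputs.** From the Sample size section: alpha 0.025 per comparison, power 90%, OR 2.67, 20-point difference, most patients at zero, at most 4 aspirations. From Randomization: 1:1:1 allocation. The splits of the non-zero counts below are assumptions.

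**1. Rates implied by the inputs.** Only two pairs combine a 20-point difference with this odds ratio:
- 40% against 20%: (0.40/0.60)/(0.20/0.80) = 2.667
- 80% against 60%: (0.80/0.20)/(0.60/0.40) = 2.667

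The second pair contradicts a majority at zero. The first leaves a mean proportion with zero of (0.60 + 0.80)/2 = 0.70.

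**2. Formula.** For a proportional-odds comparison of two equal groups, with p̄ the mean proportion in each category,

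n per group = 6(z_α + z_β)² / [(ln OR)² (1 − Σp̄³)].

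Two-sided 0.025: 6 × (2.2414 + 1.2816)² = 74.47; (ln 2.67)² = 0.9645; so n = 77.21/(1 − Σp̄³).

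**3. Trying to reproduce 112.** This needs 1 − Σp̄³ = 77.21/112 = 0.689, that is Σp̄³ = 0.311. The zero category alone contributes 0.70³ = 0.343. So no split of the non-zero counts can give 112; the floor is 77.21/0.657 = 117.5.

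**4. Particular splits.** Formula power at 112 is Φ(ln OR × √[112(1 − Σp̄³)/6] − z_α). The simulation used a tie-corrected rank (score) test with 40,000 runs.

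| Control arm, % with 0/1/2/3/4 | n, two-sided | Power at 112, formula | Power at 112, simulated | n, one-sided |
|---|---|---|---|---|
| 60/10/10/10/10 | 117.9 | 88.4% | 86.7% | 99.8 |
| 60/20/10/6/4 | 118.3 | 88.2% | 86.7% | 100.2 |
| 60/30/7/2/1 | 119.8 | 87.8% | 86.4% | 101.4 |
| 60/40 (yes/no) | 122.6 | 87.0% | 85.9% | 103.8 |

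For the one-sided column the numerator is 6 × (1.9600 + 1.2816)² = 63.05, so n = 65.37/(1 − Σp̄³). At 112 the one-sided formula power is 92 to 93%.

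**5. Other routes to 112.**
- Control-arm proportions in place of the mean: 99 to 107 two-sided, 84 to 91 one-sided.
- Two-proportion formula, 40% against 20%: 129 two-sided (138 with continuity correction), 109 one-sided (119 with correction). The 109 comes closest, but this is not the named method.
- Rounding: OR 2.675 with 20.5 points and four equal non-zero categories still gives 114.6, with formula power at 112 of about 89%.

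**6. What 112 does fit.** On the two-sided formula with non-zero counts split 50/25/15/10:
- OR 2.67 with about 43% against 22% (21 points): n = 112.4, power 89.9%.
- Control rate 40% with OR 2.75 (40% against 19.5%): 74.47/(ln 2.75)² = 72.8, and with Σp̄³ = 0.351, 72.8/0.649 = 112.

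**7. Loss.** 3 × 112 = 336, so nothing is added. If 10% were lost (an assumption; the article gives no rate), about 101 per group would remain (112 × 0.9 = 100.8), and simulated power for 40% against 20% would be about 82 to 83%.

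**The case against.** The strongest reply is that the article does not print enough to convict the number. Sidedness is not stated; under a one-sided test 112 is more than enough, and the error changes direction. The odds ratio drives an ordinal calculation, and the 20% may be only a loose translation of it. A control rate of about 43%, 3 points above the implied 40%, recovers 112 with the printed odds ratio, alpha and beta and with most patients still at zero. The upper end of the range (123 per group, 87.0% by formula) comes from collapsing an outcome that the plan treats as ordinal. The simulated figures use a different approximation from the planning formula, so they do not in themselves show an arithmetic slip.

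Much of this stands, and it rules out a stronger reading. A reader might infer that the trial is shown to be underpowered, with a true power of 87%. The article does not support that: the figure depends on a two-sided test and on a 40% control rate, neither of which is printed. Nor is power of 82 to 83% a property of the plan, since the 10% loss is assumed.

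What does not stand is that the printed inputs agree with one another. A difference of 21 points is not 20 even after rounding, and the most favourable rounding stops short of 112. A two-sided test is also the natural reading, because 0.025 is explained only as a correction for two comparisons (0.05/2) and no directional test is mentioned. The planned imputation and intention-to-treat analysis keep withdrawn patients in the analysis but do not restore the information lost with them.

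**Conclusion.** The point holds as a failure to reproduce, with a modest shortfall under the natural reading. The ordinal formula with the printed inputs gives at least 118 per group if alpha is two-sided and about 100 to 104 if one-sided; neither is 112.

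Under the two-sided reading the gap is about 6 to 11 patients per group (354 to 369 in total against 336). Power at 112 is about 2 to 3 points below 90% by formula and about 3 to 4 points below by simulation. This rests on 40% against 20%, proportional odds and complete data. The missing category proportions do not change the conclusion, because the floor of 117.5 holds for every split. The gap affects the power claim, not the validity of the planned analysis.

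**What to change.** Keep 336 patients and amend the Sample size section:

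- State whether alpha 0.025 is two-sided, the assumed control-arm rate, and the assumed distribution over 0 to 4 aspirations.
- If the test is two-sided, restate the power as about 87% for 40% against 20% (OR 2.67) with complete data. Alternatively, keep 90% and name the effect that 112 detects on the planning formula with spread counts: OR about 2.75 at a 40% control rate, or OR 2.67 at about 43% against 22%.
- Say that 336 includes no allowance for withdrawals, and label any power figure with loss as resting on an assumed loss rate.

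The cost is wording and a slightly less favourable stated power. No extra patients are needed.

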### Statistical analysis

Missing data will be imputed using stochastic regression imputation to prevent a loss of statistical precision and reduce the likelihood of biased estimates of treatment effect. Mean and standard deviation and absolute number and percentage will describe patient characteristics. Single and multiple ordinal regression analysis will be used to compute the difference in the number of seroma aspirations between the three groups. Secondary outcome parameters will be compared between groups using single and multiple ordinal regression that fits the distribution of that endpoint (e.g. continuous, binary, count). The primary analysis is an intention-to-treat analysis and therefore withdrawals and non-adherence will be analysed in the group to which they were randomized.

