### Randomization

Randomisation is achieved using a web based randomization programme (ALEA, Software for Randomisation in Clinical Trials). Randomization will take place on the day of surgery, after the start of the operation and 30 min before wound closure. Blocked randomization will take place with randomly selected block sizes (6/9/12) with an allocation ratio of 1:1:1. Randomisation will be stratified per site. Both patients and surgeons will be blinded. Patients will be blinded throughout the trial and the surgeon performing the follow-up assessments is also blinded. To ensure blinding, patients will not be evaluated by their own surgeon during follow up. Patients will be allocated into one of three groups, (A) no flap fixation and placement of a low suction drain, (B) flap fixation using sutures and placement of a low suction drain, (C) flap fixation using tissue glue (ARTISS) and placement of a low suction drain.

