### Cost effectiveness

For the economic evaluation, incremental cost-effectiveness ratios will be calculated based on the societal costs per QALY within 12 months. For calculation of the QALY, the EQ-5D-5 L will be assessed at baseline, and at postoperative visits at 6 weeks, 3, 6 and 12 months. Costs will be measured by a retrospective cost questionnaire at baseline, and at postoperative visits at 3, 6 and 12 months. Standard sensitivity analyses and non-parametric bootstrap analyses will be performed to address uncertainty about the cost-effectiveness ratio (s). Cost-effectiveness acceptability curves will be constructed to address the probability that either one of the techniques is cost-effective.

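### The only missing-data method named is stochastic regression imputation, normally a single imputation; analysed as observed data it understates standard errors, or biases the effect towards zero if arm is left out

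*Protocol article*

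**What the plan says.** The Statistical analysis section of the protocol article names one way of handling missing data: "Missing data will be imputed using stochastic regression imputation to prevent a loss of statistical precision". It gives a second purpose, to "reduce the likelihood of biased estimates of treatment effect". It states no number of imputations, pooling rule, variance correction or content of the imputation model.

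The primary analysis is fixed in the same section: "Single and multiple ordinal regression analysis will be used to compute the difference in the number of seroma aspirations between the three groups". It is by intention to treat, and withdrawals stay in their randomised group. The primary outcome is a count over the first postoperative year (Primary outcome), and patients may leave at any time (Follow up). Incomplete counts can therefore reach the primary model as imputed values.

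The Sample size section sets the error rate: "Using alpha = 0.025 (correction for 2 comparisons with 3 study groups". It also says that "the sample size is estimated at 112 patients per study group". The Cost effectiveness section adds sensitivity and bootstrap analyses, but only for the cost-effectiveness ratios.

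**The concern.** The article commits to a particular method, so this is a stated choice and not a detail left out. A single stochastic imputation preserves the spread of the data, but the later analysis cannot tell an imputed value from an observed one. Two sources of variance are then ignored: the imputed values rest on fewer observed patients, and the random draw adds noise of its own. The first stated purpose makes this worse, because a completed data set looks as precise as a fully observed one.

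At stake are the confidence intervals and the error rate for the two comparisons of flap fixation with conventional closure. The alpha was halved to protect those comparisons, and understated standard errors give part of that protection back.

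**Working it through.** **Inputs from the protocol article.** Alpha is 0.025 per comparison and beta is 0.10. The effect is a "proportional odds ratio = 2.67 (corresponding to an absolute difference of 20% in the need for seroma aspirations". There are 112 patients per group, allocated 1:1:1. The outcome is ordinal, with a maximum of 4 in the earlier retrospective study.

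**Assumptions.** Tests are two-sided, since sidedness is not stated. The missing fraction *m* is the same in each arm and missingness is completely at random. The article gives no missing rate, so a range is shown.

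**The plan's own figures.** Rates of 40% and 20% give an odds ratio of (0.4/0.6)/(0.2/0.8) = 2.667, which matches 2.67. The 112 per group can be neither confirmed nor refuted, because the category proportions are not given. The proportional-odds formula gives 118 to 119 for plausible five-category spreads built on 40% versus 20%, and 112 for other spreads. The point below does not depend on it.

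**Arm in the imputation model, no predictive covariates.** Let one arm have *n* patients and outcome variance s².

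- Mean of the observed patients: variance s²/[n(1−m)].
- Random residuals for *mn* imputed patients: added variance m²·s²/(mn) = m·s²/n.
- True variance: (s²/n)[1/(1−m) + m]. The analysis reports s²/n.
- Variance ratio: V = 1/(1−m) + m. The standard error is understated by the factor √V.
- Actual type I error: 2[1 − Φ(2.2414/√V)], where 2.2414 is the two-sided critical value for 0.025.

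| m | V | √V | Type I error, formula | Type I error, simulated |
|---|---|---|---|---|
| 2% | 1.040 | 1.02 | 0.028 | not run |
| 5% | 1.103 | 1.05 | 0.033 | 0.032 |
| 10% | 1.211 | 1.10 | 0.042 | 0.041 |
| 15% | 1.326 | 1.15 | 0.052 | 0.053 |
| 20% | 1.450 | 1.20 | 0.063 | 0.060 |

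The simulation used 40,000 null trials with 112 per arm and five categories with assumed probabilities 0.60, 0.20, 0.10, 0.06 and 0.04. The test was the proportional-odds score test (tie-corrected Wilcoxon). Complete cases in the same trials gave 0.024 to 0.027.

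**Arm in the model, with predictors.** If covariates or partial counts explain a share R² of the outcome, V = 1 + (1−R²)[m/(1−m) + m].

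| m | R² = 0 | R² = 0.5 | R² = 0.8 |
|---|---|---|---|
| 5% | 0.033 | 0.029 | 0.027 |
| 10% | 0.042 | 0.033 | 0.028 |
| 20% | 0.063 | 0.043 | 0.032 |

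For example, at m = 10% and R² = 0.5: V = 1 + 0.5(0.1111 + 0.1) = 1.106, √V = 1.051, and 2.2414/1.051 = 2.132, which gives 0.033. The R² values are assumptions.

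**Arm left out of the imputation model.** Simulated type I error stayed at 0.024 to 0.025. The effect is attenuated instead, because missing values in both arms are drawn from the pooled distribution. Take 80% and 60% of patients without aspiration, so 70% pooled. At m = 10% the completed data show 0.9×80 + 0.1×70 = 79% and 0.9×60 + 0.1×70 = 61%. The difference falls from 20 to 18 points, and the odds ratio from 2.67 to (0.79/0.21)/(0.61/0.39) = 2.41. At m = 20% the difference is 16 points and the odds ratio (0.78/0.22)/(0.62/0.38) = 2.17.

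**The case against.** The strongest reply is that the article does not say the data are filled in once and then treated as observed. That comes from the standard meaning of the term, and an analysis plan not shown here could specify repeated draws with pooling. This stands as a limit: the consequence is conditional. It does not remove the point, because the only method named is a single-imputation method and nothing stated corrects its variance.

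Other objections also stand in part:

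- **Size.** The larger figures need a wholly missing outcome and no predictors. Visits at 2 and 6 weeks and at 3, 6 and 12 months leave partial counts for patients who drop out late, and data queries (Data management) may keep missingness low.
- **Unconditional inflation.** A reader might infer that the type I error must exceed 0.025. It need not: if arm is omitted the error is kept, and the harm is bias.
- **The precision rationale.** A reader might infer that imputation can save no precision. Compared with discarding patients, it can, by using partial counts or keeping patients with a missing covariate. It cannot restore the precision of a fully observed sample.
- **Impossible counts.** A reader might infer fractional or negative imputed aspiration counts. The article does not say that the imputation regression is linear, so this is not supported.
- **Cost-effectiveness.** A reader might infer that those uncertainty intervals will certainly be too narrow. The article does not say whether imputation is repeated inside the bootstrap, and no size was computed.

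**Conclusion.** The point holds in conditional form and should be fixed before analysis; it does not by itself invalidate the trial. If the completed data are analysed as observed, either choice about arm causes harm. With arm included, standard errors are understated and the type I error rises in the worst case to about 0.028, 0.033, 0.04 and 0.06 at 2%, 5%, 10% and 20% missing. With R² = 0.5 it is about 0.029 at 5% and 0.033 at 10%. At 2% missing the effect is negligible. In the worst case at 15% missing, the per-comparison error is about 0.05, which undoes the halving of alpha. With arm omitted, the absolute difference shrinks in proportion to the missing fraction.

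These sizes rest on assumed missing rates, assumed predictive strength, two-sided testing and missingness completely at random. The direction rests only on the named method being used in its usual sense, with no correction for the imputed values.

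**What to change.** Replace the method with multiple imputation. Include arm, site, axillary clearance, baseline values and outcomes recorded before dropout in the imputation model. Use an ordinal or predictive-mean-matching model for the aspiration count, and pool with Rubin's rules. If costs and QALYs are imputed, carry the imputation uncertainty into the bootstrap. Report complete cases as a sensitivity analysis. Reword the precision rationale to say that imputation uses the available partial information, and not that it restores full-sample precision.

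If the analysis plan already pools repeated draws with arm in the model, it is enough to correct the sentence in the protocol.

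The cost is slightly wider confidence intervals and a little more analysis work. No new data and no change of design are needed.

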Until now one prospective randomized controlled trial has been published showing a significant reduction of seroma formation and seroma related complications after flap fixation using quilting sutures [21]. A review published by Van Bastelaar et al. concluded that mechanical flap fixation seems to reduce seroma formation and seroma aspiration after mastectomy with or without axillary clearance. Well executed randomized controlled trials are however needed to confirm these results [22]. The aim of the current randomized controlled trial (RCT) is to compare seroma formation and its sequelae in the various methods of flap fixation. The SPIRIT Statement guidelines were used for designing and describing this trial [23, 24].

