## Discussion

A number of retrospective trials were performed to demonstrate that flap anchoring and therefore dead space reduction could be very beneficial. Until now one prospective randomized controlled trial has been published showing a significant reduction of seroma formation and seroma related complications after flap fixation using quilting sutures. A review published by Van Bastelaar et al. concluded that mechanical flap fixation seems to reduce seroma formation and seroma aspiration after mastectomy with or without axillary clearance. Well executed randomized controlled trials are however needed to confirm these results and to compare the different flap fixation techniques [22]. Furthermore, no cost-effectiveness analyses have been performed on this topic yet. One other multi center randomized controlled trial (QUISERMAS) is currently being conducted in France to assess the effect of quilting of the dead space after mastectomy on seroma prevention [25]. However patients and surgeons are not blinded to the closure technique used. Moreover patients undergoing mastectomy without axillary clearance in the conventional closure group receive a drain, while the patients in the quilting group are not drained. This may potentially bias the study outcomes and therefore we chose to perform.

a double-blinded study. Furthermore, the QUISERMAS trial does not include a study arm analysing the application of tissue glues. Cosmetic results in the QUISERMAS study will be assessed by an independent adjudication committee. Finally, in our study we decided to let patients assess cosmesis themselves as we consider their opinions as being most important in evaluating outcome. This is the first study of its kind to evaluate the effect of flap fixation and its sequelae (ie seroma aspirations, number of out patient clinic visits, infection, shoulder function, patient assessed cosmesis, quality of life and cost-effectiveness) in a double-blind randomized controlled trial.

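### Alpha is corrected for two unnamed comparisons, while the aim and the three-group analysis also take in sutures versus glue, which has no share of alpha and no stated status

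*Protocol article*

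**What the plan says.** Four places in the protocol article bear on this.

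- **Study objectives.** The primary objective concerns the effect of fixation by sutures or by glue on the number of aspirations. It reads most naturally as each technique against conventional closure, which makes two comparisons.
- **Sample size.** "Using alpha = 0.025 (correction for 2 comparisons with 3 study groups), beta = 0.10", with "a proportional odds ratio = 2.67 (corresponding to an absolute difference of 20% in the need for seroma aspirations", leads to 112 patients per group and 336 in all. The two comparisons are not named.
- **Abstract and Background.** The aim of the trial "is to compare seroma formation and its sequelae in the various methods of flap fixation". Taken literally, this is method against method.
- **Statistical analysis.** Ordinal regression will "compute the difference in the number of seroma aspirations between the three groups". No contrasts are singled out.

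Nowhere is sutures versus glue given a significance level, an assumed effect, or a label as confirmatory or exploratory.

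**The concern.** Three arms give three pairwise comparisons. The correction covers two. The third, sutures versus glue, lies within the stated aim and within the three-group analysis sentence, but outside the error budget.

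Two things are at stake. First, a claim that one technique beats the other would not sit under the 5% familywise limit that the correction is meant to protect. Second, if the comparison turns out non-significant, its status and its precision matter. With no stated status, such a result could be reported as if the trial had settled the question, although 112 per arm gives a wide interval for the difference between two techniques that both work.

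**Working it through.** **Inputs from the protocol article:** alpha 0.025 per comparison, power 0.90, proportional odds ratio 2.67 for a 20-point difference, 112 per arm, 1:1:1 allocation, counts from 0 to 4. **Assumptions:** two-sided tests (sidedness is not stated), and 40% v 20% needing aspiration, because (0.4/0.6)/(0.2/0.8) = 2.67. The split of counts 1 to 4 is not given, so a range is shown.

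**1. The plan's own figure.** Whitehead's formula is n per arm = 6(z_α + z_β)² / [(ln OR)²(1 − Σp̄³)], where p̄ are the mean category proportions of the two arms. Here 6(2.2414 + 1.2816)²/(0.9821)² = 77.2. Dividing by 1 − Σp̄³ gives:

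- control 60/40% (binary): 77.2/0.630 = 122.6
- control 60/20/10/6/4%: 77.2/0.652 = 118.3
- control 57/20/12/6/5%: 77.2/0.688 = 112.3

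So 112 is attainable under a nearby assumption, with 0.025 taken as two-sided. It cannot be reproduced exactly without the category proportions.

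**2. Familywise error.** For equal arms, the pairwise z statistics that share an arm have correlation 0.5 in absolute value. With critical value 2.2414 (4 million simulated trials):

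- two contrasts with conventional closure at 0.025: 4.6%, within 5%
- all three pairs at 0.025: 6.4% (the studentized range gives the same; the Bonferroni bound is 3 × 0.025 = 7.5%)

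The 6.4% arises only when all three arms are equal. If exactly one pair is equal, there is one true null hypothesis and its error is 2.5%.

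**3. Power and precision for sutures versus glue, 112 per arm, two-sided 0.025.** The two-proportion formula for 20% v 10% gives z = [0.10√112 − 2.2414√(2·0.15·0.85)] / √(0.16 + 0.09) = (1.058 − 1.132)/0.5 = −0.147, so power is 44%. The same formula gives 27% for 20% v 12% and 10% for 20% v 15%. If one method stays at the control level (40%) and the other reaches 20%, the odds ratio is again 2.67 and power equals that of the design contrasts. If both are truly at 20%, the 95% CI for the difference is ±1.96√(2·0.2·0.8/112) = ±10.5 points.

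**4. Flat 0.025 against Holm, when both techniques work at OR 2.67.** Normal approximation with a shared control arm:

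| Control split (%) | Each contrast: flat → Holm | Both contrasts: flat → Holm |
|---|---|---|
| 60/40 | 87.0 → 90.6 | 78.7 → 86.0 |
| 60/20/10/6/4 | 88.2 → 91.6 | 80.6 → 87.4 |
| 57/20/12/6/5 | 89.9 → 93.0 | 83.1 → 89.3 |

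The gain is 3 to 4 points per contrast and 6 to 7 points for both.

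**5. Error of Holm with a gatekept third test.** If all arms are equal, any false claim needs a first Holm rejection at 0.025: 4.6%. If only one technique equals conventional closure, the single true null hypothesis is tested at no more than 0.05. If both techniques work equally well, the only possible false claim is sutures versus glue, tested at 0.05. Simulation over these configurations gave at most about 5.0%.

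**The case against.** The best defence is that the document already has a coherent two-comparison reading. The primary objective points to each technique against conventional closure, and the correction is for exactly two. A regression with conventional closure as reference category yields exactly two treatment coefficients. On that reading 0.025 is right. A condensed article may also leave contrasts and testing order to the full protocol or analysis plan.

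Much of this stands. The two contrasts with control are properly protected, and not repeating the 0.025 in the analysis section is no fault. The Discussion's phrase "to compare the different flap fixation techniques" describes what the literature needs, not a planned test, so it carries no weight here. Bonferroni is also a valid method, and preferring Holm corrects no error.

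What remains is that the article itself fixes a correction for two comparisons beside a method-versus-method aim and an analysis across all three groups. Even the two-comparison reading leaves sutures versus glue without a status.

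Three stronger readings are tempting and not supported:

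- *All three pairs would be tested at an uncorrected 0.05.* The Sample size section states 0.025, so this requires ignoring it.
- *Sutures versus glue is simply not powered.* Any pair separated by the design odds ratio from the control level has the design power. Power is low only for smaller absolute differences between two methods that both work.
- *The trial intends to claim equivalence of the two techniques.* No section says so. The interval width only shows why a null result should not be read that way.

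**Conclusion.** The mismatch is real and moderate. The correction suits two contrasts with conventional closure; the aim and the three-group analysis reach a third that has neither alpha nor status. If it were tested at 0.025 beside the other two, familywise error would be about 6.4% instead of at most 5%, and only when all three arms are equal. The larger practical issue is interpretation: about 44% power for 20% v 10%, and an interval of about ±10.5 points if both techniques are at 20%.

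The power and precision figures assume two-sided tests and 40% v 20% as the meaning of the odds ratio. The Holm gains assume control distributions with 57% to 60% of patients at zero. The familywise figures concern multiplicity across arms only and leave the planned interim analysis aside. The point deserves correction but does not threaten the two main comparisons.

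**What to change.** State in the Statistical analysis section:

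1. The primary family is sutures versus conventional closure and glue versus conventional closure, tested by Holm at overall two-sided 0.05: the smaller p-value against 0.025 and, if that succeeds, the larger against 0.05.
2. Sutures versus glue is tested at two-sided 0.05 only if both primary contrasts are significant.
3. Otherwise sutures versus glue is reported as an estimate with a 95% CI, with no claim of superiority or equivalence.

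The Abstract and Background aim should be worded to match. The cost is text only: no extra patients, and Holm rejects whenever the flat 0.025 rule does. By comparison, splitting alpha equally over three pairs (0.05/3 = 0.0167) and keeping 90% power would need about 122 per arm, scaling 112 by [(2.394 + 1.282)/(2.241 + 1.282)]² = 1.088.
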